## Abstract

**Background:**

Heart failure (HF) significantly impacts on the daily lives of patients and their carers. In Western society HF education programs have increased patient and carer knowledge and improved health-related quality of life. However, there is a paucity of such evidence in Asia. For example, to date no studies have been conducted in Thailand to investigate the potential benefits of a family-based education program on the health outcomes of HF patients and carers.

**Methods:**

This randomised controlled trial will evaluate the effectiveness of an education program on knowledge, self-care and health-related quality of life of Thai HF patients and their carers. Assessments will be conducted at baseline, three and six months. Participants will be assigned by independent random allocation to an intervention (family-based education plus usual care) or a control (usual care) group. Analyses will be conducted on an intention-to-treat basis.

**Discussion:**

This trial will be the first to evaluate the effectiveness of family-based education for HF patients and carers residing in rural Thailand. It attempts to advance understanding of family-based HF education and address the gap in service provision.

**Trial registration:**

Thai Clinical Trial Registry TCTR20140506003

## Background

Over 23 million people worldwide suffer from heart failure (HF) [1]. Already at epidemic proportions, this significant global public health problem is predicted to escalate exponentially over the next decade [1]. For example, currently in the United States HF affects over five million people [2] and it is expected that by 2030 eight million will be diagnosed with HF [3]. Heart failure is now one of the most common reasons for hospital admissions in older people, resulting in a substantial economic drain on healthcare resources [4].

One way to redress the burden of HF is through implementation of multidisciplinary chronic disease models of care that have been shown to yield significant benefits, compared with usual care, in reducing readmissions and associated costs and improving patient quality of life [5]. Identified as a key component of these programs is patient education specifically directed at promoting self-care behaviours [6]. Most studies investigating HF patient education have been conducted in Europe [7–10], Australia [11–13] and North America [14–17]. This leaves a significant knowledge gap regarding the efficacy of such programs in Asia, for example Thailand.

The Thai Acute Decompensated HEart Failure REgistry (Thai ADHERE) has recognised HF as a major cardiovascular health problem and economic burden [18]. Thai ADHERE epidemiological data were collected from 18 cardiovascular health centres across Thailand. Thai ADHERE found 2,041 HF admissions among 1,612 HF patients during 2006 to 2007. A large proportion of re-hospitalisations were admitted via the emergency department (77%), of which one quarter (25%) required a critical care bed. The absence of HF education programs was identified as a significant factor leading to the high numbers of Thai HF readmissions [18]. Evidence presented from studies conducted in Western countries has demonstrated that many HF readmissions are preventable through patient education targeting self-care [6, 19].

Patient education aims to improve knowledge and skills in order to positively influence attitudes and behaviours, thereby resulting in improved health outcomes [20]. Knowledge can improve an individual’s confidence and sense of control, and with respect to understanding the disease trajectory of HF, can motivate patients to adhere to treatment and lifestyle changes and necessary adaptations [21]. The evidence-base in support of patient education improving HF health outcomes is compelling [5, 6, 22], and has resulted in the inclusion of educational strategies as a key non-pharmacological component within evidenced-based HF practice guidelines [4, 23, 24].

The situation-specific theory of HF self-care provides a framework for understanding and evaluating the competencies of HF patients [25]. Self-care refers to a naturalistic decision-making process involving the choice of behaviours patients adopt in order to maintain physiological stability and responses executed when they occur [26]. Appropriate engagement in HF self-care has the potential to reduce HF readmissions and health care costs, and improve health-related quality of life [27]. In light of this, evidence has also revealed that patients with HF demonstrate difficulties in complying with the recommended self-care regimen [28]. Recently, and importantly, patient knowledge and social support from informal carers are fast being recognised as key to successful self-care [29–32].

The informal carer can be defined as a spouse/partner, family member, friend or neighbour who performs caring without pay, assisting the care recipient with daily activities and/or medicine administration [33]. The role of carers is crucial in HF self-care. A recent systematic review found that the social well-being of HF patients is strongly linked with carers’ support in performing HF self-care [29]. Social support has been found to be a vital resource for patients with HF and used as part of their everyday coping strategies [32]. Patient health outcomes, including health-related quality of life (HRQoL), rehospitalisation, adherence to HF treatment, and optimal engagement in self-care, are strongly associated with the existence of carers [34]. International guidelines now specify that carers be included in the educational processes that promote HF self-care [35–37], though the number of intervention studies that have focused on informal carers of HF are limited [38].

Although the evidence is compelling as to the importance of patient education promoting self-care, most studies investigating patient education have been conducted in Europe, Australia and North America where the characteristics of the population and the culture are often quite different from that in Asia, including Thailand, and especially in rural communities. In Thailand only one published randomised trial of education (coaching by telephone) in HF has been conducted [39], and only two other published studies have explored the notion of education improving knowledge, self-care and HF symptoms [40, 41]. However, limitations of these studies include the use of quasi-experimental designs, small samples, differing theoretical frameworks for developing the educational strategies, and varied settings - home-based to outpatient clinic settings – for conducting them. Moreover, none of these studies included carers, or delivered the education program in the community, nor examined changes in HRQoL in both the patient and carer as an outcome of the education. In light of the incomplete body of knowledge regarding the effectiveness of an education-based intervention for HF patients and carers in Thailand, and the increasing prevalence of HF in Thailand, further research is warranted.

Cultural perspectives become paramount when adapting a Western-based intervention into an Asian country. For example, in Thailand the role of carer is crucial, and the Buddhist concept of karma strongly influences Thai people’s beliefs and their way of thinking and living. Although demographic and socio-economic aspects have changed dramatically in Thailand over recent decades, family members remain the pillar of support for elderly people [42]. Living with older parents, showing respect and taking care of them are considered a normal way of family life and are highly valued in Thailand. Therefore, providing an education program that involves both the patient and carer has the potential to enhance the quality of life for the patient with HF, and for their supporting family [43].

### Aim

The aim of this research is to develop and evaluate a family-based education program for HF patients and their carers residing in rural Thailand.

### Hypothesis

We hypothesise that a family-based education program is effective in improving HF knowledge, self-care behaviour and HRQoL for patients, and perceived control, HF knowledge and HRQoL for their carers living in rural Thailand.

## Methods

### Study design

This is a prospective single-blind randomised controlled trial of family-based education versus usual care for HF patients and their partners residing in rural Thailand. Ethics approval has been obtained from the Human Research Ethics Committees of the Australian Catholic University and Chumphon Hospital and informed consent will be obtained from all participants prior to enrolment. The trial will be conducted in accordance with CONSORT (Consolidated Standards of Reporting Trials) guidelines ([44] See Figure 1).

**Figure 1 Fig1:**
[figure not shown]
**Study design, flow of participant.**

The setting will be outpatient clinics at one provincial hospital and one community hospital in Chumphon province in the south of Thailand. These clinics were purposively selected on the basis that they are representative of HF patients and care in the rural community. Participants will be assigned by independent random allocation to an intervention (family-based education plus usual care) or a control (usual care) group.

### Participant eligibility

Participants for this study will be a dyad consisting of a patient and their partner or family member that is identified as providing informal care. All participants will need to have sufficient comprehension to read Thai without the need for a translator. The patients will be aged 20 years or over, although with the increasing prevalence of HF in the elderly, it is envisaged that the majority will be above 50 years of age. The inclusion criteria for HF patients are: 1) a primary diagnosis of HF NYHA (New York Heart Association) class I to III confirmed by the treating doctor and determined by a history of typical signs and symptoms and physical examination [45] and, where possible, objective evidence of cardiac dysfunction on echocardiogram; 2) at least one family member residing with them; 3) contactable by telephone at home; and 4) a DVD player at home. The inclusion criteria for carers are: 1) living in the same household as the HF patient or someone of the patient’s own choice; and 2) aged 20 years or over. Participants will be excluded if they reside in an urban area, have a documented history of dementia or severe psychiatric illness, are unable to continue to follow the protocol, and have severe symptoms indicative of acute heart failure [24, 46] or complications from cardiac or disease or other life threatening comorbidities.

### Recruitment

This trial will enroll a minimum of 100 dyads sourced from two rural hospitals in Thailand. Participants will be identified for enrolment by clinical staff based on inclusion criteria. Potential dyads will be approached at their regular outpatient appointment or contacted via telephone and verbally informed of the study. The dyads who agree to participate will receive a verbal and written explanation of the study by the investigator or the attending nurse, allowing them time to consider and freely participate.

### Randomisation

The investigator will derive the random allocation from a computer-generated sequence of random numbers. Each dyad will be randomised at a 1:1 ratio in blocks of ten to either the control (usual care) or intervention (family-based education plus usual care) group. The random allocation will be sealed in an envelope and retained by technical staff at each hospital to give to the research assistants. Once participants have consented to the study and baseline data has been collected, the research assistant will open the sealed envelope indicating the group allocation. In this way, the research assistant collecting baseline data will be unaware of which group participants have been allocated to.

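### The investigator derives the allocation sequence and may also explain the study to prospective dyads, which conflicts with the stated independent allocation

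*Protocol article*

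**What the plan says.** All references are to the protocol article.

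- **Claim of independence.** The study design text states: "Participants will be assigned by independent random allocation to an intervention" or a control group. The Methods part of the abstract makes the same claim.
- **Who makes the list.** Randomisation: "The investigator will derive the random allocation from a computer-generated sequence of random numbers".
- **Block size.** Randomisation: "Each dyad will be randomised at a 1:1 ratio in blocks of ten". No other size is given.
- **Who finds and informs dyads.** Recruitment: "Participants will be identified for enrolment by clinical staff based on inclusion criteria". Dyads who express agreement then "will receive a verbal and written explanation of the study by the investigator or the attending nurse", and have time to think before taking part.
- **Concealment.** Randomisation: "The random allocation will be sealed in an envelope and retained by technical staff at each hospital to give to the research assistants". A research assistant opens the envelope once consent and baseline data are in hand.
- **Later contact.** Under Intervention group and Process evaluation, the principal investigator makes telephone calls to participants. That person therefore learns allocations as enrolment proceeds.

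**The concern.** Concealment works only if nobody who can influence whether or when a dyad enters knows what the next assignment will be. The article gives the making of the list to the investigator and names the investigator as one of two people who may explain the study. If the same person does both, that person could encourage, discourage or postpone a dyad in the light of the coming allocation, without any lapse in the handling of the envelopes.

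The stake is selection bias in a trial whose primary patient outcome is a knowledge score. Literacy and motivation plausibly affect such a score, and a recruiter can sense both in conversation. Some of this could be examined afterwards: baseline questionnaires are completed before randomisation, and education level and health literacy are recorded. Unmeasured differences such as motivation could not be adjusted for.

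**Working it through.** **1. Role conflict (no arithmetic).** The tasks, with the role that the article assigns to each:

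| Task | Role named | Section |
|---|---|---|
| Derive the sequence | The investigator | Randomisation |
| Identify candidates | Clinical staff | Recruitment |
| Explain the study | The investigator or the attending nurse | Recruitment |
| Hold the envelopes | Technical staff at each hospital | Randomisation |
| Open the envelope | Research assistant, after consent and baseline | Randomisation |
| Follow-up telephone calls | The principal investigator | Intervention group; Process evaluation |

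The first and third rows name the same role. Nothing in the article bars the list's author from explaining the study, or withholds the list from those who do. The envelope steps separate the holder from the opener and delay opening, so they protect against people who do not already know the sequence. They do nothing about someone who does. That is the conflict with the claim of independence, and it does not depend on block size.

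**2. Block of ten (secondary).** The article gives no predictability figure, so there is none to reproduce. Inputs: 1:1 ratio and block size 2m = 10, so m = 5. Assumption: the observer knows the block size, the block boundaries and every earlier assignment in the block.

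- Expected number of allocations certain in advance per block: 2m/(m+1) = 10/6 = 1.67 of 10, or 16.7%.
- Expected number of correct guesses when always naming the arm with more places left: m + 4^m/(2·C(2m,m)) − 0.5 = 5 + 1024/(2 × 252) − 0.5 = 6.53 of 10, against 5 by chance.

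An exact recursion over the permuted block gives the same values. For other fixed and known sizes it gives:

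| Block size | Certain in advance | Best guess correct |
|---|---|---|
| 4 | 33.3% | 70.8% |
| 6 | 25.0% | 68.3% |
| 8 | 20.0% | 66.6% |
| 10 | 16.7% | 65.3% |
| 20 | 9.1% | 61.7% |

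Ten is thus less predictable than the smaller sizes. Its weakness is that it is a single size and is in print. For someone who has the list itself, every allocation is knowable and this table is irrelevant.

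**The case against.** The strongest reply is that the article describes sensible concealment: sealed envelopes, custody by staff with no stated recruiting role, opening only after consent and baseline, and identification of candidates by clinical staff. The explanation goes to dyads who have already shown willingness, and the nurse may be the one who gives it. Recruitment and Randomisation speak only of the investigator, while other sections speak of the principal investigator, so these need not be the same person. All of this stands, and it limits what can be concluded. It does not remove the overlap that the text allows, because the dyad still has time to consider after the explanation.

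Several stronger readings are tempting and are not supported:

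- *One person is shown to foresee every assignment.* This requires that a single investigator does both tasks, gives the explanation in place of the nurse, keeps the list and can match it to the next envelope. The article states none of these.
- *About 17 of 100 dyads will have predictable assignments.* Ten blocks at 1.67 each do give 16.7, but only for an observer who sees every assignment and knows the boundaries. Two hospitals recruit, and the article does not say whether they share a list or whether recruiters are told the block size.
- *Opening by research assistants is a defect.* They act after consent and baseline, and no section gives them a say in who joins. Opening at that point is how concealment should work.
- *Envelope opacity, numbering or separate hospital lists are missing.* A condensed article may leave such details to the full protocol.

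**Conclusion.** The point holds as a conflict between sections. The article calls the allocation independent, yet it lets the role that derives the sequence take part in the consent conversation, and the envelopes cannot conceal the sequence from its author. This rests on the wording alone, read as permitting the overlap and not as proving that it will occur. The size of any resulting bias cannot be estimated from the document.

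The fixed block of ten is a minor supporting point. The figures of 1.67 in 10 certain and 6.53 in 10 guessed are an upper bound for a fully informed recruiter who does not hold the list. By itself, the choice of ten would not call for a change. The role conflict does, because it is cheap to remove before enrolment and cannot be reliably undone afterwards where the differences are unmeasured.

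**What to change.** Amend the Randomisation section so that the sequence is generated and the envelopes are prepared by an existing colleague with no role in recruitment, intervention or assessment. State that the list is withheld from everyone who recruits, including the investigator and the attending nurse. The claim of independent allocation in the abstract and the study design text would then be accurate as it stands.

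As a secondary step, let that colleague vary the block sizes at random and keep them undisclosed until enrolment closes. Non-disclosure matters: as the table above shows, small sizes that become known are more predictable than ten.

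The cost is a sentence or two of text and a little of a colleague's time, with no extra procedure for dyads or hospitals. The small statistical price is that balance may be slightly looser at a given moment. At 100 dyads, for example, ten full blocks of ten on one list would give exactly 50 and 50, whereas mixed sizes may end part-way through a block.

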#### Data analyses and sample size calculation

Data collected will be entered into the Statistical Package for the Social Sciences (SPSS Inc.). Descriptive statistics will be used to analyse demographic data. The sample size calculation is based on changes in HF knowledge. In a previous study investigating HF knowledge as the primary outcome [22]), a sample size of 50 per group and allowing for a 10% attrition rate, had adequate power (0.80) with a two-sided 95% significance to detect a difference of two-points on the DHFKS between the intervention and control conditions in mean post-test versus pre-test changes on the DHFKS and 93% power to detect clinically significant difference in MLHF scores of 6-points. For this study, assuming a medium effect size (0.65) in the between-group differences on the DHFKS and allowing for a 20% attrition rate, the minimal sample size of 40 per group will have sufficient power (0.80). An independent t-test will be used to test the overall differences of the DFHKS, SCHFI, CAS, MLHF and SF-12 within the groups and between the control group and the intervention group at baseline and over three and six months. Two-way repeated measures analysis of variance (ANOVA) will be used to test the difference between groups and change overtime in each group of the main outcomes (DFHKS, SCHFI, CAS, MLHF and SF-12). Treatment failure and withdrawal will be considered on an intention-to-treat basis, with the aim of providing a more realistic estimate of the difference between the two groups.

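### Hospital is absent from the stated t-tests and ANOVA although allocation is blocked and held at each of two unlike hospitals: a small, nearly free gain in precision is left unused

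*Protocol article*

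**What the plan says.** All references are to the protocol article.

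- **Sites.** Study design places the trial in clinics at "one provincial hospital and one community hospital in Chumphon province". Recruitment sets the size: "This trial will enroll a minimum of 100 dyads sourced from two rural hospitals in Thailand".
- **Allocation.** Randomisation states "Each dyad will be randomised at a 1:1 ratio in blocks of ten to either the control (usual care) or intervention", from a computer-generated sequence. On custody it says "The random allocation will be sealed in an envelope and retained by technical staff at each hospital". It does not say whether each hospital has its own list or whether one list is divided between them.
- **Analysis.** Data analyses and sample size calculation states "An independent t-test will be used to test the overall differences" on all five instruments, between groups, at baseline, three and six months. It adds a two-way repeated measures ANOVA whose factors are group and time. Hospital is not a factor, covariate or stratum in either.
- **Sample size.** The same section bases the size on change in heart failure knowledge, "assuming a medium effect size (0.65) in the between-group differences on the DHFKS" and "allowing for a 20% attrition rate", with 40 per group for power 0.80.

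**The concern.** Blocking within hospital makes the arms nearly equal at each site, so a difference between hospitals cannot contribute much to the difference between arms. A plain t-test does not use this. It leaves the between-hospital variance in its error term and so overstates the uncertainty of the estimate.

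If the list is not stratified, the t-test's standard error is correct on average. The arms may then differ by chance in hospital mix, and the hospital variance remains noise that could have been removed.

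Usual care is delivered by clinicians at a provincial and a community hospital, so a difference in scores is plausible, although no figure is given. At stake is some power in a trial expecting about 80 evaluable dyads, and agreement between the way dyads are allocated and the way they are analysed.

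**Working it through.** **The plan's own figure.** Inputs are a standardised difference of 0.65 and power 0.80, with two-sided 5% assumed (the article gives it only for the earlier study it cites).

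- n per group = 2(1.960 + 0.842)² / 0.65² = 37.2, so 38. Allowing for 20% loss: 38 / 0.80 = 47.5, so 48.
- The 100 dyads give 50 per arm, and 50 × 0.80 = 40. The stated 40 per group is therefore read as the number analysed. Power at 40 is 0.828 by normal approximation and 0.819 by the noncentral t. The plan's figure reproduces.

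**Blocks within hospital.** Let D be the difference in mean outcome between hospitals in total SDs, and p the share of dyads at one hospital. D is an assumption. With 40 per arm:

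- share of variance due to hospital: R² = p(1 − p)D²
- reported SE / true SE = 1/√(1 − R²)
- z₀ = 0.65/√(2/40) = 2.907
- power without a hospital term = Φ[(z₀ − 1.960)/√(1 − R²)]
- power with a hospital term = Φ[z₀/√(1 − R²) − 1.960]
- actual type I error without the term = 2Φ[−1.960/√(1 − R²)]

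For p = 0.5:

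| D | R² | SE too large by | Type I error | Power without | Power with |
|---|---|---|---|---|---|
| 0 | 0 | 0% | 0.050 | 0.828 | 0.828 |
| 0.25 | 0.016 | 0.8% | 0.048 | 0.830 | 0.834 |
| 0.5 | 0.062 | 3.3% | 0.043 | 0.836 | 0.851 |
| 0.75 | 0.141 | 7.9% | 0.035 | 0.846 | 0.880 |
| 1.0 | 0.250 | 15.5% | 0.024 | 0.863 | 0.919 |

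A 70:30 split gives slightly less: 0.835 against 0.848 at D = 0.5, and 0.857 against 0.905 at D = 1.0.

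Measuring the difference in within-hospital SDs instead gives R² = (D²/4)/(1 + D²/4) = 0.059, 0.123 and 0.20 at 0.5, 0.75 and 1.0. Standard errors are then 3%, 7% and 12% too large.

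**Simulation** (100 dyads, blocks of ten, 20% random loss, 10,000 runs per scenario):

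- *Blocks within hospital, D = 0.5.* Mean reported SE is 0.224 against a true SD of the estimate of 0.216 to 0.220. Type I error is 0.046. Power is 0.833 without and 0.851 with a hospital term.
- *Blocks within hospital, D = 1.0.* SE is 0.224 against about 0.20. Type I error is 0.029. Power is 0.846 without and 0.913 with the term. Random loss disturbs the balance within hospital, so the SE excess is smaller than in the table.
- *One unstratified list.* The reported SE agrees with the true SD (0.224 against 0.225 to 0.228 at D = 1.0). Power still rises with a hospital term: 0.818 to 0.839 at D = 0.5, and 0.818 to 0.908 at D = 1.0.

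**Change scores and group-by-time.** If hospital adds the same constant at baseline and follow-up, it subtracts out of each dyad's change. A simulation of change scores with a constant gap of 1.0 SD gave power 0.822 without and 0.823 with a hospital term, and type I error 0.05 both ways.

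The table and the 100-dyad simulation describe a single-timepoint comparison. The ANOVA group main effect is affected in the same direction, but its size was not calculated separately.

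**The case against.** **Standard errors too large as a fact.** A reader might infer that the planned standard errors are simply wrong. The documents do not support this. It needs blocks generated within each hospital, which custody of envelopes at each site suggests but does not state. It also needs a real difference in outcome, for which no figure is given. With one unstratified list the t-test is valid, and a hospital term is ordinary covariate adjustment.

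**The hospitals may be alike.** The article calls both hospitals rural, says the clinics were chosen as representative of rural patients and care, applies the same eligibility criteria at both and excludes urban residents. None of this shows equal outcomes, but nothing supports a gap of 0.75 or 1.0 SD either. The lower rows of the table are the safer guide.

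**The comparison that sized the trial.** The sample size rests on change in knowledge, where a constant hospital difference cancels. This stands. The loss is confined to the t-tests on scores at three and six months and the ANOVA group main effect, unless change itself differs by hospital.

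**A failed or biased trial.** A reader might also infer lost power against plan or false positives. Neither follows: unadjusted power stays at about 0.82 or more in every scenario with 40 evaluable per arm, and any error is conservative.

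**Detail left to an analysis plan.** Covariates are often settled there, and one not shown might add hospital. That carries weight for how the list is generated. It carries less for the tests: the article names them, a plain t-test has no place for a hospital term, and the two ANOVA factors are given as group and time.

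**Conclusion.** This is a worthwhile, nearly free improvement and not an error in the plan. Allocation is blocked with envelopes at each of two unlike hospitals, and the named tests make no use of hospital.

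With 40 evaluable per arm and blocks within hospital, the power gain from a hospital term is nil at 0 SD, about 0.5 points at 0.25 SD, 1 to 2 at 0.5 SD, about 3 at 0.75 SD and 5 to 7 at 1.0 SD. With an unstratified list it is about 2 points at 0.5 SD and 9 at 1.0 SD. All of this rests on an assumed hospital difference, a roughly even split of dyads and single-timepoint comparisons. Little is gained for change scores or the group-by-time test unless change differs by hospital. The stated power of 0.80 is not undermined, and there is no excess of false positives.

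**What to change.** 1. In Randomisation, state that a separate blocked list is generated for each hospital, if that is the intention. If one list is to be divided between the sites, say so.
2. In Data analyses and sample size calculation, replace the plain between-group t-test with a linear model containing group and hospital as fixed factors. Add hospital as a between-subject factor in the repeated measures model, alongside group, time and group-by-time.

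The cost is one phrase, one model term and one degree of freedom. Hospital is already known for every dyad. If the hospitals do not differ, the simulated price is negligible with blocks within hospital (power 0.817 without, 0.816 with) and under one point with an unstratified list (0.821 without, 0.814 with). The change should be made before outcome data are seen, so that results cannot influence the choice of model.

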#### Data collection

Before randomisation all dyads will complete baseline questionnaires. Outcome measures will be collected at three and six months at the outpatient clinic or via telephone interview. Data will be collected by research assistants who are not aware of study group allocation. Questionnaires will take approximately 45 to 60 minutes to complete.

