#### Process evaluation

Ongoing monitoring of program activity in both the intervention and control group will be regularly conducted. Participants will be interviewed when the principal investigator performs a telephone follow-up. Participants in the control group will be asked how satisfied they are with regular telephone contact. The investigator will pilot test the DVD and HF manual in six HF patients and carers prior to implementation of intervention, to ensure their usability and refine if necessary. Participants in the intervention group will be asked how satisfied they are with the DVD and the HF manual and telephone follow-up. At the end of the program participant satisfaction will be measured using a visual analogue scale and participants will be invited to offer additional comments. Completion of activities in the HF manual will be assessed by viewing participants’ HF manual at the six-month assessment. This process assessment is integral to identifying cultural and social facilitators of, and barriers to, the process of lifestyle behaviour change to improve HF risk as a result of this educational intervention.

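### The protocol claims blinded follow-up assessment but does not secure it: the role that opens the allocation envelope is also the role declared unaware of allocation when outcomes are collected

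*Protocol article*

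**What the plan says.** The Study design section describes a "prospective single-blind randomised controlled trial" and does not name the blinded party there.

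Under Randomisation, the sealed allocation is "retained by technical staff at each hospital to give to the research assistants". After consent and baseline data collection, "the research assistant will open the sealed envelope indicating the group allocation". The stated benefit is that "the research assistant collecting baseline data will be unaware of which group participants have been allocated to".

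Under Data collection, "Outcome measures will be collected at three and six months at the outpatient clinic or via telephone interview", and the next sentence adds: "Data will be collected by research assistants who are not aware of study group allocation".

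Under Process evaluation, completion of the manual's activities is judged by looking at each participant's "HF manual at the six-month assessment". The Control group section offers the DVD and manual to control participants only when the six-month follow-up has ended.

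**The concern.** One job title carries two roles that do not fit together. Research assistants receive the envelopes and read the allocation; research assistants are also the people said not to know it when they collect the three- and six-month outcomes. The reason given for the envelope procedure covers baseline only, whereas the treatment effect is measured at follow-up.

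This matters because the research assistants are the only people whom the article describes as unaware of allocation. Dyads know whether they attended an education session and were given a manual and DVD. The principal investigator makes the teach-back calls to the intervention group and so must know the arm. If the assistants are not blind at follow-up, nothing else in the article supports the single-blind label.

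All the outcomes, including the two primary ones (DHFKS in patients, CAS in carers), are questionnaire scores. An assessor who knows the arm could prompt or clarify differently between groups, and the trial report would claim a safeguard that may not have been in place.

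**Working it through.** The blinding question is one of text, so the sections are set side by side first.

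| Step | Who | Knows the arm? | Section |
|---|---|---|---|
| Hold sealed envelopes | Technical staff at each hospital | No, while sealed | Randomisation |
| Collect baseline | Research assistant | No | Randomisation |
| Open envelope after baseline | Research assistant | Yes, from then on | Randomisation |
| Intervention telephone calls | Principal investigator | Yes | Intervention group |
| Three- and six-month outcomes | Research assistants | Declared no | Data collection |
| View manual at six months | Not stated | Sight of the manual reveals the arm | Process evaluation |

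1. Rows three and five are compatible only if the assistant who opens a dyad's envelope never collects that dyad's follow-up data. The article does not state this condition.
2. The timing rule (open after baseline) makes row two safe. It has no bearing on row five.
3. In the last row, control dyads have no manual until follow-up ends, so a manual presented at the six-month assessment marks an intervention dyad. Neither the viewer nor the order relative to the questionnaires is given.

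**Group size for an illustration.** The plan has 40 per group, effect size 0.65, power 0.80 and 20% attrition. Two-sided 5% is stated for the earlier study and assumed to carry over.

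- n = 2 × (1.960 + 0.842)² / 0.65² = 2 × 7.849 / 0.4225 = 37.2, so 38 per group (39 with the t distribution), close to the stated 40 if that means evaluable participants.
- 38 / 0.80 = 47.5, so 48 per group enrolled. This is consistent with the minimum of 100 dyads, or 50 per group, and 50 × 0.80 = 40 evaluable.

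The sample size is not in question here; it only fixes the group size used below.

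**What an assessor bias could do.** The documents give no figure, so the bias b (in SD units, between groups) is an assumption shown over a range. With no true effect, SE = √(2/m) and the two-sided error rate is 1 − Φ(1.96 − b/SE) + Φ(−1.96 − b/SE).

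| Assumed b | m = 40 (SE 0.224) | m = 50 (SE 0.200) |
|---|---|---|
| 0 | 5.0% | 5.0% |
| 0.1 | 7.3% | 7.9% |
| 0.2 | 14.5% | 17.0% |
| 0.3 | 26.9% | 32.3% |

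For example, b = 0.2 and m = 40 give b/SE = 0.894 and 1 − Φ(1.066) + Φ(−2.854) = 0.145. The table shows how sensitive the test would be to a bias of each size. It is not evidence that such a bias would occur.

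**The case against.** The best defence is that both sections refer to research assistants in the plural and that the trial runs at two hospitals. Data collection makes an explicit commitment, and taken at its word it requires whoever collects a dyad's outcomes not to know its arm. Which assistant does which task is delegation detail that a condensed article may leave to the full protocol. On this reading there is no contradiction, only something unsaid.

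Part of this stands. A reader might infer that the claimed blinding is not delivered, or that every follow-up assessment is unblinded. The documents do not support that, because they nowhere say that one person does both tasks. The point nevertheless goes beyond missing detail: the article chose to describe the envelope procedure, and that procedure reveals the arm to the only role it calls blind.

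A reader might also infer that the primary outcomes are wholly interviewer-dependent, or that the results must lean towards the intervention. That goes too far as well. The DHFKS is a self-report questionnaire of 15 multiple-choice items, the CAS has eight items with fixed five-point responses, and all participants must be able to read Thai, so self-completion at the clinic is feasible. Fixed responses leave little room for lenient scoring. Prompting remains possible, chiefly by telephone.

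On the manual, Process evaluation names no viewer. Viewing by the principal investigator, or after the questionnaires, would fit the text and need not unblind an assessor. What stands is that the text permits the harmful order as readily as the harmless one.

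**Conclusion.** The concern holds in a limited form. The protocol asserts blinded outcome assessment at three and six months without securing it: the role that opens the envelope is the role declared blind, post-baseline opening protects baseline only, and viewing the manual at six months is a second way for the arm to become known.

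The size of any resulting bias is unknown. The error rates above rest on an assumed bias, a normal approximation and 40 or 50 evaluable per group. How many assessments are exposed depends on staffing and on the split between clinic and telephone collection, neither of which is given. No sample-size figure changes.

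It should be settled before follow-up begins, because an assessor's blinding cannot be restored once the allocation has been seen.

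**What to change.** - **Randomisation and Data collection:** state that anyone who has opened or seen a dyad's allocation does not collect that dyad's three- or six-month outcomes. Have the envelope opened, after consent and baseline are confirmed complete, by existing staff who do not assess outcomes. The technical staff who already hold it are one option; they would then inform whoever delivers the session, a person whom the article does not name. Concealment before allocation is unchanged.
- **Process evaluation:** have the manual viewed, and the arm-specific satisfaction questions asked, only after that dyad's six-month questionnaires are complete and by someone other than the outcome assessor.
- **Study design:** name the outcome assessors as the blinded party. If the separation cannot be kept at either hospital, restate the single-blind description accordingly.

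The cost is procedural wording and some coordination of hand-overs at two hospitals. It uses existing staff and needs no extra visits or additional participants.
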